### Data collection

A nurse researcher enrolls the older patients according to the inclusion and exclusion criteria and collect demographic data at admission, including sex, age, ethnicity, education level, marital status, smoking, and drinking. Clinical data includes diagnosis of major diseases, visual acuity level, hearing level, cognitive function, physical function, depression, and comorbidity. The mini-mental state examination (MMSE) is used to assess cognitive function, the total score is 0–30, and a higher score indicates better cognitive function [30]. The Geriatric depression scale (GDS-15) is used to assess depression, the overall score is 0–15, with less than 8 indicating depression [31]. The Charlson comorbidity index (CCI) is used to assess the comorbidity index, and a higher score indicates more underlying diseases in older people [32]. The Modified barthel index (MBI) is used to assess the activities of daily living at admission by the nurse researcher, and a higher score indicates better mobility. Restraint use during hospitalization will also be recorded [33].

The delirium assessment data will be stored in a smartphone with 3D-DST installed, and the data can be exported. Patients' general and clinical data is collected using questionnaires, and the data will be input into SPSS by two researchers and checked for errors. The data is stored by the investigator and is confidential before, during and after the trial. Only the investigators responsible for the outcome collection and supervisors of this study have access to the data according to the protocol.

Prior to the study, a study group is established, all adverse events will be reviewed regularly by the researchers, and a meeting of the researchers will be convened if necessary to assess the risks and benefits of the study. All adverse events will be recorded in detail, properly handled, and followed up until the adverse events are properly resolved. Serious adverse events will be reported to the ethics committee and authorities according to regulations.

### Statistical analysis

SPSS 22.0 (SPSS Inc., Chicago, Illinois, USA) will be used for statistical analysis. Multiple imputation will be used to fill in missing data using the R software. A *P*-value of 0.05 will be defined as statistically significant. The continuous data will be tested for normality and homogeneity of variance by the "One-Sample Kolmogorov Smirnov Test" and the "Homogeneity of Variance Test". Mean and standard deviation (SD) will be used for normally distributed continuous variables, median and interquartile range (IQR) will be used for continuous variables with non-normal distribution. The rank sum test and *t*-test will be used to compare the demographics and clinical characteristics of different groups. Categorical variables will be expressed in frequency and percentage, and the Chi-square test or Fisher's Exact Test will be used for comparing variables between different groups. The effects on clinical outcomes will be analyzed by a generalized linear mixed model. Subgroup analysis will be performed to eliminate the effect of confounding factors (age, gender, education level, comorbidity, marital status, smoking, drinking, cognitive function, physical function, depression, and comorbidity). Data will be analyzed according to the per-protocol principle. The preliminary analysis will be conducted after the start of the study (three months, one year, close-out).

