### Cluster randomization and blinding

Before randomization, the wards that participated in the study will be pair matched according to the specialty. Within each of the two pairs, wards will be randomly assigned (1:1) to the intervention or control group using random numbers generated by the computer, which indicates that each group will contain one neurology and one respiratory ward. The medical staff who will be involved in the study only know the protocol of their ward, but not be aware of the protocol of other wards and the hypothesis of the study. Due to the allocation sequence generating, participants’ enrollment, participants’ assignment, data and outcome collection will be done by a nurse researcher, therefore the protocol will not be blinded to the nurse researcher. However, the nurse researcher and the bedside nurse will be unaware of each other's assessment results of delirium.

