### Sample size

The primary outcome is delirium duration. We expect that the delirium duration of the intervention group will be one day shorter than that of the control group, with a standard deviation of 1.8 [28], α of 0.05, and intraclass correlation coefficient of 0.00001. Our study will be estimated to provide more than 80% power, at least five delirium-positive patients in each group (ward), and 20 delirium-negative patients will be needed. According to our previous study, the incidence of delirium is approximately 10%, with an estimated 10% of patients dropping out during the study, at least 202 older patients will be needed. Patients will be given a detailed explanation of the benefits they will receive from participating in the study to reach the target sample size.

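### Subgroup analysis is given the task of removing confounding, but it yields no adjusted overall effect; adjust the mixed model for a few baseline factors instead

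*Protocol article*

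**What the plan says.** The Statistical analysis section of the protocol article names the outcome model in one sentence: "The effects on clinical outcomes will be analyzed by a generalized linear mixed model". It gives no fixed effects or covariates for that model. The next sentence turns to confounding: "Subgroup analysis will be performed to eliminate the effect of confounding factors". The factors follow in brackets: "age, gender, education level, comorbidity, marital status, smoking, drinking, cognitive function, physical function, depression, and comorbidity". That is eleven entries, of which ten are distinct.

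The Data collection section shows that all ten are recorded. The nurse researcher will "collect demographic data at admission, including sex, age, ethnicity, education level, marital status, smoking, and drinking", and "Clinical data includes diagnosis of major diseases, visual acuity level, hearing level, cognitive function, physical function, depression, and comorbidity". The instruments named there include the MMSE, the Charlson index and the modified Barthel index.

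Two parts of the design bear on how much imbalance to expect. Under Cluster randomization and blinding, four wards are matched by specialty, and "Within each of the two pairs, wards will be randomly assigned (1:1) to the intervention or control group", so each arm has one neurology and one respiratory ward. The same section says that one nurse researcher generates the sequence, enrols the patients and collects the outcomes, "therefore the protocol will not be blinded to the nurse researcher".

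**The concern.** The sentence names a method and a purpose, and the two do not match. This is a stated rule, not a detail left for a later document, and an analyst who followed it would run the wrong analysis for the stated aim.

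Imbalance is a realistic prospect here. Randomizing two wards per arm leaves patient case mix largely to chance. Enrolment by someone who knows the allocation also allows selection to differ between arms. If confounding control is left to subgroups, the trial would report a series of small, separate contrasts, none of which is an adjusted estimate of the effect on delirium duration. Some of those contrasts could reach 0.05 by chance.

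**Working it through.** **The plan's own figures.** The dispute is about method, so no stated number is contested. The Sample size section supplies the inputs: a difference of one day, SD 1.8, alpha 0.05 (taken as two-sided, since sidedness is not stated), at least five delirium-positive patients per ward, 10% incidence, 10% dropout and 202 patients.
- Delirium-positive patients: 4 wards × 5 = 20, or 10 per arm. From the total, 202 × 0.9 × 0.1 = 18.2, so 18 to 20 is a fair working range.
- The stated power above 80% is not reproduced with 10 per arm. The standardized difference is 1/1.8 = 0.556 and the noncentrality is 0.556 × √(10/2) = 1.24, which gives 24% (normal) or 22% (t). That is a separate sample-size matter, but it sets the baseline for the subgroup figures below.

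**What one-factor subgroups do to confounding.** Assume a binary factor present in 35% of one arm and 55% of the other, adding one day to the outcome, with no true treatment effect. These values are assumptions, not from the documents.
- One such factor: unadjusted bias = 1 × (0.35 − 0.55) = −0.20 day. Within each level of the factor the bias is 0.
- Two independent factors of this kind: unadjusted bias = −0.40 day. Splitting on the first leaves −0.20 day from the second inside each subgroup. A model containing both gives 0.
- A simulation of these settings (4,000 runs, 101 per arm, residual SD 1.8, no clustering) agreed. With one factor, the subgroup estimates had standard errors of 0.35 and 0.40 day, against 0.26 for the adjusted model over all patients. With two factors, the one-factor subgroup estimate was −0.20 (standard error 0.40) and the adjusted estimate 0.00 (0.27).

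The size of the bias depends on the assumed imbalance. The pattern does not.

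**Splitting on all ten together.** Two levels each gives 2^10 = 1,024 cells, and 202/1,024 = 0.2 patients per cell. This is not feasible.

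**Illustrative precision and multiplicity.**
- If duration is compared only in about 20 delirium-positive patients, an even split leaves about five per arm. The noncentrality is 0.556 × √(5/2) = 0.88. For the effect in the Sample size section, where "the delirium duration of the intervention group will be one day shorter than that of the control group", power is about 12% (t, 8 df) or 14% (normal).
- If each of ten factors were tested once at 0.05 and the tests were independent: 1 − 0.95^10 = 0.40. If each factor gave two subgroup tests: 1 − 0.95^20 = 0.64.

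**Room for covariates.** If duration is analysed only in 18 to 20 delirium-positive patients, an intercept, treatment, specialty and ten single-parameter covariates use 13 parameters and leave 5 to 7 residual degrees of freedom. With four covariates the count is 7 parameters, leaving 11 to 13.

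**The case against.** The strongest reply has four parts.

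*The subgroup sentence is not the plan's only protection.* This is correct. A reader might infer that nothing else guards against imbalance, but matching by specialty and computer randomization within pairs are both stated, and the Discussion presents the pairing as a way to reduce bias. That protection covers specialty. It does not balance age, cognition, function or comorbidity between two wards and two wards.

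*The mixed model may be adjusted.* A reader might infer that the primary estimate will stay confounded. The article does not support that: it leaves the model unspecified, and a covariate list is commonly held in the full protocol or analysis plan. The silence is no finding. What remains is the next sentence, which assigns confounding control to a different method.

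*Stratification does remove confounding by the stratifying factor.* True within levels, as the one-factor case shows. It would be too strong to say that subgrouping has no effect on confounding. The shortfall is that the other nine factors remain and no overall adjusted effect results.

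*The magnitudes are conditional.* They are. The article does not clearly restrict duration to delirium-positive patients, gives five per ward as a minimum, and does not say that every factor is halved and tested. Subgroup tests on the same patients are also correlated, so 40% and 64% are not estimates for this trial. Much of the low subgroup power reflects the small number of delirium-positive patients overall, which is a separate matter.

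**Conclusion.** The point holds in limited form and should be corrected. Subgroup analysis, as stated, does not do what the sentence claims: taken one factor at a time it leaves nine of ten listed factors uncontrolled and yields no single adjusted effect, and taken jointly it is impossible with 202 patients. This conclusion rests on the quoted sentence and on arithmetic, with no assumption about the unseen analysis plan.

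The document does not show that the primary estimate will be biased, or by how much. The bias of −0.20 to −0.40 day comes from assumed imbalances, and the 12%, 40% and 64% figures rest on the conditions given with them.

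The remedy has a limit too. Patient-level covariates reduce measured patient-level imbalance. They cannot remove confounding by ward characteristics with two wards per arm: four wards, less intercept, treatment and specialty, leave one ward-level degree of freedom.

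**What to change.** Replace the subgroup sentence with wording such as:

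> *The generalized linear mixed model for the primary outcome will include specialty (the matching pair) and a short prespecified set of baseline covariates (for example age, MMSE, Charlson index, modified Barthel index) as fixed effects. A small number of prespecified subgroups will be examined by treatment-by-factor interaction tests; these are exploratory and are not intended to control confounding.*

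Then:
- State that adjustment addresses measured patient-level imbalance only and cannot remove ward-level confounding with two wards per arm.
- Keep the covariate set short, above all if duration is analysed only in the roughly 20 delirium-positive patients. The four covariates are examples; the trial team should choose them on prognostic grounds before seeing outcome data.
- Confirm that each covariate is an admission value. The Data collection section ties demographics and the modified Barthel index to admission explicitly, but does not give a time for the MMSE. A score taken after delirium has begun would not be a baseline covariate.
- Delete the duplicate entry for comorbidity.

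The cost is a change of wording in the protocol or analysis plan. The listed factors are already collected, and no change to sample size or trial conduct is needed.

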Therefore, we hypothesize that the use of the 3D-DST will improve the adherence to delirium assessment and management by clinical staff, and reduce the duration and the severity of delirium.

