### Design and setting

This study is a pair-matched, open-label, parallel, cluster randomized controlled superiority trial with a 1:1 allocation ratio. Cluster randomization minimizes group contamination and accounts for intraclass correlation [22]. Four medical wards (two respiratory and two neurology wards) of a geriatric hospital in China will be invited to participate in the study. The neurology and respiratory wards receive approximately 20 and 40 older adults per month, respectively. This study was registered on the Chinese Clinical Trial Registry (registration number: ChiCTR1900028402).

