### Adherence/termination

As the adherence of medical staff in implementing the interventions is one of the outcomes of this study, the researchers will not intervene in the adherence of medical staff. If participants choose to withdraw, transfer out of the ward, die, or discharge, they will stop receiving the interventions. The reason will be recorded if the patient fails to complete the evaluation during the evaluation period.

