### Study outcomes

Delirium positive is defined as the occurrence of delirium assessed by a nurse researcher using the 3D-DST. Enrolled patients will be assessed twice daily for delirium by a nurse researcher using the 3D-DST for the same period of time as the nurses in the wards. Delirium duration, delirium severity, incidence of delirium, length of stay, in-hospital mortality, delirium assessment, delirium prevention, and treatment interventions performed by medical staff will be recorded by the nurse researcher.

The primary outcome of the study is delirium duration: defined as the number of delirium positive days in older adults between admission and death/transfer from the ward.

Secondary outcomes include six aspects.The severity of delirium: defined as the score of the CAM-S scale evaluated by the nurse researcher.Delirium incidence: defined as the percentage of delirium-positive patients accounting for the total number of included patients from admission to death/transfer out of the ward who were assessed by the nurse researcher using the 3D-DST.Length of stay: defined as the total number of of hospital days from admission to the day of death/transfer.Mortality rate: defined as the percentage of patients who died during hospitalization account for the total number of enrolled patients.The rate of adherence to delirium assessment: defined as the number of delirium assessments by the nurse as a percentage of the number of theoretically required assessments between patient’s admission and death/transfer out of the ward.The rate of adherence to delirium prevention and treatment: defined as the number of preventive and treatment interventions implemented by nurses and clinicians as a percentage of the number of theoretically required interventions between patient’s admission and death/transfer from the ward.

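### Per protocol is the only analysis principle stated, and its set is undefined, in an open-label cluster randomised superiority trial; the comparison as allocated is lost

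*Protocol article*

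**What the plan says.** All places are in the protocol article.

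- **Statistical analysis:** "Data will be analyzed according to the per-protocol principle". This covers all data. No intention-to-treat or as-allocated analysis appears anywhere, and the per-protocol set is not defined. The same paragraph adds: "Multiple imputation will be used to fill in missing data using the R software".
- **Design and setting:** "This study is a pair-matched, open-label, parallel, cluster randomized controlled superiority trial with a 1:1 allocation ratio".
- **Introduction:** "we hypothesize that the use of the 3D-DST will improve the adherence to delirium assessment and management by clinical staff".
- **Study outcomes:** Adherence to assessment is a secondary outcome: "The rate of adherence to delirium assessment: defined as the number of delirium assessments by the nurse as a percentage of the number of theoretically" required. Adherence to prevention and treatment is defined in the same way. Incidence is taken over all included patients and mortality over all enrolled patients.
- **Adherence/termination:** The researchers will leave staff adherence alone: "As the adherence of medical staff in implementing the interventions is one of the outcomes of this study". The section also names patient-level exits: "If participants choose to withdraw, transfer out of the ward, die, or discharge, they will stop receiving the interventions". The reason is recorded when a patient does not complete the evaluation.

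**The concern.** In a superiority trial the main comparison should keep each patient in the arm to which the ward was allocated. A per-protocol set drops patients because of what happened later. Those who remain in one arm need not be comparable with those who remain in the other, and a difference between arms may then reflect who was kept.

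This trial has two features that make the choice riskier than usual. It is open label, and one nurse researcher who knows the allocation enrols the patients and collects the outcomes. With no definition of the set, exclusions could be decided with knowledge of the arm. Staff adherence is also both the route by which the tool is meant to work and an outcome in its own right, so any exclusion based on adherence would bear directly on the effect under study.

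This is not detail left to an analysis plan. The article fixes the principle, and a later plan would have to contradict it to repair it.

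**Working it through.** **1. What could define the set.** The article gives no rule, so two readings are possible.

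| Reading | Basis in the article | Consequence |
|---|---|---|
| A. Patients who left or did not complete the evaluation are excluded | Exits and incomplete evaluation in Adherence/termination; 10% dropout in Sample size | Selection on events after allocation |
| B. Patients whose bedside assessment or care fell short are also excluded | No sentence says so; it is one ordinary meaning of per protocol | Selection on a mediator that the Introduction expects to differ by arm; close to circular for the adherence outcomes |

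Reading A already loses the comparison as allocated. Reading B adds to the harm: removing non-adherent cases before comparing adherence removes the variation to be measured.

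**2. Fit with the rest of the text.** Incidence and mortality are defined over all included or enrolled patients, and a per-protocol set would shrink those denominators. Multiple imputation normally serves to keep incomplete patients. It can be run inside a per-protocol set, so this is a tension and not a contradiction.

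**3. Is the primary outcome available without the exclusions?** Delirium duration comes from the nurse researcher's own twice-daily assessments. A bedside assessment missed by ward staff therefore does not make the primary outcome missing, and patients with poor staff adherence can be analysed.

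**4. Possible size of the bias (illustration).** The article gives no retention or adherence figures by arm, so there is no figure of its own to reproduce.

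Inputs:
- From Sample size: SD 1.8 days, and "We expect that the delirium duration of the intervention group will be one day shorter than that of the control group".
- Assumed: no true effect; a standard normal prognostic factor U with correlation 0.5 with duration; probability of being kept 1/(1 + exp(−(a − bU))), with b from 0.5 to 1.0 and a set to give the retention shown. Patients with a worse prognosis are thus less likely to be kept.

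Formula: shift in mean duration in an arm = 0.5 × 1.8 × E[U | kept] = 0.9 × E[U | kept].

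| Retained | E[U given kept], b = 0.5 | E[U given kept], b = 1.0 |
|---|---|---|
| 90% | −0.049 | −0.091 |
| 80% | −0.096 | −0.173 |
| 70% | −0.143 | −0.253 |
| 60% | −0.189 | −0.332 |
| 50% | −0.236 | −0.413 |

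Spurious difference, intervention minus control, with 90% kept in the intervention arm:

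| Control retention | b = 0.5 | b = 1.0 |
|---|---|---|
| 90% | 0.00 day | 0.00 day |
| 80% | 0.9 × (0.096 − 0.049) = 0.04 | 0.9 × (0.173 − 0.091) = 0.07 |
| 70% | 0.9 × (0.143 − 0.049) = 0.08 | 0.9 × (0.253 − 0.091) = 0.15 |
| 60% | 0.9 × (0.189 − 0.049) = 0.13 | 0.9 × (0.332 − 0.091) = 0.22 |
| 50% | 0.9 × (0.236 − 0.049) = 0.17 | 0.9 × (0.413 − 0.091) = 0.29 |

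Analysis of all patients as allocated gives 0 in every row. A positive value works against the intervention. The sign reverses if patients with a worse prognosis are more likely to be kept.

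**The case against.** The strongest defence is that the exclusion rule is not stated. No sentence says that a patient is removed because staff missed an assessment or an intervention. Adherence/termination points the other way: adherence is an outcome and is left free to vary, so staff non-adherence may not be a protocol deviation at all. The departures actually named concern the patient. A reader might infer that the plan removes poorly managed patients, and so selects on the mediator and differently by arm. The document does not support that as a statement of fact; it holds only under reading B. This part of the objection stands.

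Death and transfer are also built into the observation windows in Study outcomes, so patients with those events need not be lost. That stands too, but it helps the plan little: outcome definitions that run to death or transfer, with all-enrolled denominators, belong with an analysis of everyone.

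A reader might further infer that per protocol contradicts the multiple imputation, or that patients with missed assessments are known to differ in severity. Imputation inside a per-protocol set is possible, and the article says nothing about the severity of such patients.

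The objection does not rescue the stated principle. Withdrawal and incomplete evaluation also arise after allocation, and leaving the set undefined in an open-label trial with an unblinded outcome collector adds to the problem.

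**Conclusion.** The concern holds in this form: per protocol is the sole, undefined principle for all data in an open-label cluster randomised superiority trial, and it loses the comparison as allocated. It also sits badly with the article's own denominators and, less sharply, with its imputation plan. This rests on the text and needs no numerical assumption.

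Selection on the mediator, and near-circularity for the adherence outcomes, are conditional on staff non-adherence counting as a deviation.

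The size and direction of the bias cannot be derived from the document. The 0.00 to 0.29 day range rests on the assumed correlation, selection strength and retention rates. It shows that the bias vanishes when both arms lose patients alike, and that it can reach a noticeable fraction of the 1-day target when they do not.

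**What to change.** Replace the per-protocol sentence with:

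> All enrolled patients will be analysed in the arm to which their ward was allocated, whatever the adherence of staff. Multiple imputation applies to missing nurse-researcher outcome assessments and baseline covariates; bedside assessments or interventions not done count as not done in the adherence outcomes and are not imputed. A per-protocol analysis, with its set defined in advance, is supportive only and is not used for the adherence outcomes.

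The second sentence is needed because a missed bedside assessment is itself the adherence result; imputing it would corrupt that outcome.

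**Cost:** a short amendment. No new data are needed and the target of 202 is unchanged. The estimated effect may be smaller than under per protocol. Trial status reports enrolment as ongoing, so the change can still precede the final analysis.
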